### Assignment of interventions: blinding

#### Who will be blinded {17a}

Patients or personnel involved in the trial cannot be blinded to the treatment conditions due to the nature of the intervention. The outcome measurements are objective and are on-line registered in an automatic patient data management system, PDMS. Only data analysts will be blinded.

#### Procedure for unblinding if needed {17b}

The design is open label with only data analysts being blinded therefore unblinding will not occur.

### Data collection and management

#### Plans for assessment and collection of outcomes {18a}

Baseline characteristics of the participants will be collected. Data such as age, gender, height, weight, medical history and ASA-classification, will be obtained from the medical record. Data from during sedation such as heartrate, blood pressure, bispectral index (BIS), duration of PSA and duration of procedure will be obtained from the anaesthesia record (on-line automatic patient data management system, PDMS). The ISAS questionnaires [4] is a validated questionnaire that measures patient experience with monitored anaesthesia care. Patients respond to eleven statements (e.g. I felt pain) by placing a six-choice vertical response column (e.g. “disagree, moderate”).

#### Plans to promote participant retention and complete follow-up {18b}

Patients will receive an email after a week if they didn’t response to the questionnaire invitation. All other data are recorded during admission.

#### Data management {19}

Data management system Castor will be used for data storage and the eCRFs. All research data is stored encrypted in the database so the privacy of the participants is ensured. Members of the research team will have access to the source documents with personally identifiable information. All patients will receive a Castor ID. This Castor ID is composed of any numbers of figures, not based on age, date of birth, name or gender (e.g. 000001, 000002, 000003). The key to the code is safeguarded by the research team in the source document. A monitor and national supervisory authorities e.g. IGJ can access the data to control the research team. The handling of personal data will comply with the EU General Data Protection Regulation and the Dutch Act on Implementation of the General Data Protection Regulation (in Dutch: Uitvoeringswet AVG, UAVG).

#### Confidentiality {27}

The key to the code is safeguarded by the research team in the source document. Without authorization one cannot access the source document. Only the research team has authorization to access the source document with personally identifiable information.

#### Plans for collection, laboratory evaluation and storage of biological specimens for genetic or molecular analysis in this trial/future use {33}

Not applicable because there are no biological specimens in this study.

### Statistical methods

#### Statistical methods for primary and secondary outcomes {20a}

##### Primary outcome

The primary outcome parameter is the lowest SpO_2_. SpO_2_ is a continuous variable and will be presented as mean and standard deviation (SD). Univariable between-group analysis using the independent-samples *t*-test will be performed. To adjust for potentially confounding variables, we will perform multiple linear regression analysis. Covariates will be age, gender, BMI, ASA-classification, duration of RFCA procedure, hypotension and BIS. We will impute missing data using multiple imputation with fully conditional specification. The number of imputations will be set to the percentage of incomplete records. All analyses will be performed according to the intention-to-treat principle. All participants who are randomised are included in the statistical analysis and analysed according to the group originally assigned to, regardless of the treatment received.

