### Trial design {8}

This study is a single centre, randomised controlled trial and is designed to evaluate the superiority of HFNC compared with LFNC. Based on a power-calculation {14}, it is aimed to include 188 participants. The allocation ratio is 1:1. Patients will be randomised to the intervention group (HFNC during deep sedation) or the control group (LFNC during deep sedation). Figure 1 summarises the study design.

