### Assignment of interventions: allocation

#### Sequence generation {16a}

The allocation of participants to groups will be randomised using computer-randomised allocations (data management system used: Castor). Sequence generation will be performed in blocks of 2,4,6 stratified by gender.

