##### Secondary outcomes

Cross over of therapy is a binary categorical variable. We will compare the difference in cross-over between groups using Pearson’s chi-squared test. The analysis of the incidence of hypoxemia is performed either with logistic or Poisson regression depending on the distribution. All continuous variables like area under the curve SpO_2_, ISAS score, mean TcCO_2_ and peak TcCO_2_ will be presented as group mean and SD. Univariable analysis using the independent-samples *t*-test will be performed. Further analysis will be done using multiple linear regression. Covariates will be specified as age, gender, BMI, ASA-classification, duration of RFCA procedure, hypotension and BIS. The occurrence of adverse events will be presented as count and percentage per group. Analysis will be performed using a logistic regression model. Likert type questions will be reported as percentage of patients that scored each of the options, stratified by group. The median for central tendency and frequencies for variability are calculated for analysing these descriptive statistics. The response on the Likert type questions will be analysed separately for each question using the Mann-Whitney *U* test.

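### Lowest SpO2 is analysed by an unadjusted t-test and by a regression without a stated order; a single baseline-adjusted model that includes the gender stratum would settle this and gain precision

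*Protocol article*

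**What the plan says.** The trial is "designed to evaluate the superiority of HFNC compared with LFNC" (Trial design {8}), and "The allocation ratio is 1:1". Under Sequence generation {16a}, "Sequence generation will be performed in blocks of 2,4,6 stratified by gender".

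Under Statistical methods {20a}, Primary outcome, two analyses of lowest SpO2 follow one another: "Univariable between-group analysis using the independent-samples *t*-test will be performed. To adjust for potentially confounding variables, we will perform multiple linear regression analysis". For the second, "Covariates will be age, gender, BMI, ASA-classification, duration of RFCA procedure, hypotension and BIS". Gender therefore enters the regression but not the t-test. Neither analysis is called primary, confirmatory, supportive or sensitivity.

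Three other places bear on the order:

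- Sample size {14} gives 94 per group from a calculator for two independent means, which is an unadjusted comparison.
- Statistical methods {20a}, Secondary outcomes, repeats the same pair of tests for the continuous outcomes and introduces the regression there as a further step.
- The section on additional analyses {20b} plans none, so the regression is not placed there as an extra.

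**The concern.** Two analyses of one endpoint can give p-values on either side of 0.05. If the text does not say which one carries the superiority claim, that choice can be made after both are seen. Blinding the analyst to arm does not prevent this, because both p-values are visible whichever arm is which.

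There is also a question of efficiency. If the t-test is the main test, it is the one that leaves out the stratification factor. Stratified blocks remove most of the between-gender variation from the difference in means, but the pooled SD of the t-test still contains it, so the standard error is somewhat too large. Age, BMI and ASA class are collected at baseline in any case and would be unused in the main comparison. The stated reason for adjustment is confounding. Randomisation already deals with that in expectation, and the gain from baseline covariates in this design is precision.

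**Working it through.** **Step 1. The plan's own figure.** Inputs from Sample size {14}: means 95.2% and 99.3% (difference 4.1 points), SD printed as 0.1, power 80%, alpha 0.05 (taken as two-sided), 94 per group.

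n per group = 2 × (1.960 + 0.842)² × (SD/difference)². With the SD read as a proportion (10 points): 2 × 7.85 × (10/4.1)² = 93.4, so 94. Power at 94 per group is 80.3%. The figure reproduces for an unadjusted two-sided comparison. (The scale of the printed SD is a separate matter.)

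**Step 2. Level of the t-test when gender is balanced by design.** Let g be the share of outcome variance explained by gender. The documents do not give it; 1% to 5% is assumed. The true variance of the difference is (1 − g) times what the t-test estimates, so

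level = 2 × [1 − Φ(1.96/√(1 − g))].

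- g = 1%: 1.96/0.995 = 1.970, level 4.9%
- g = 5%: 1.96/0.975 = 2.011, level 4.4%

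The error is on the conservative side.

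**Step 3. Power of a baseline-adjusted model.** Let R² be the share of variance explained by baseline covariates. It is not in the documents; 5% to 30% is assumed. At 80% power the t-test has expected z = 1.960 + 0.842 = 2.802. The adjusted test has expected z = 2.802/√(1 − R²), and power = Φ(2.802/√(1 − R²) − 1.96).

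**Step 4. Disagreement and the either-test error.** The two statistics are treated as bivariate normal with correlation √(1 − R²). The probabilities below come from that distribution.

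| Assumed R² | Correlation | Power, adjusted model (t-test 80%) | Tests disagree, at that effect | Type I error if either may be claimed |
|---|---|---|---|---|
| 5% | 0.975 | 82% | 5% | 6.0% |
| 10% | 0.949 | 84% | 7% | 6.5% |
| 20% | 0.894 | 88% | 11% | 7.1% |
| 30% | 0.837 | 92% | 14% | 7.6% |

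**Step 5. Cross-check by simulation.** N = 188, 1:1 within gender strata (124 and 64, an assumed split), gender plus six other baseline-type covariates, gender explaining 1% to 5%, standardised effect 0.41. There were 12,000 null runs and 6,000 runs with the effect per scenario. For R² of 5/10/20/30%:

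- either-test error: 6.0/6.6/7.0/7.1%
- disagreement at the planned effect: 6/7/11/13%
- power of the adjusted model: 81/82/86/91%
- level of the t-test: between 4.4% and 4.9%

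The two routes agree closely.

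**Limit of steps 3 to 5.** They describe a model with baseline covariates only. The planned regression also contains procedure duration, hypotension and BIS, which arise after randomisation and may be affected by the arm. The planned pair of analyses may therefore estimate different effects, and could disagree more often than shown.

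**The case against.** The strongest reply is that the order is clear enough. The trial was sized for an unadjusted comparison of two means, the t-test comes first, and for the continuous secondary outcomes the regression is introduced as a further step. The natural reading is t-test as the main test and regression as support, and a statistical analysis plan that is not shown may say so. This largely stands. A missing label alone would be a detail that the analysis plan can supply, and naming the t-test would by itself remove the ambiguity. What remains is that the method so implied is the less efficient one, and a better one is available from data already collected.

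Three stronger readings are tempting, and the documents do not support them:

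- A reader might infer that the trial's type I error is above 5%. That requires permission to claim superiority on whichever test succeeds, and the text gives none.
- A reader might infer that ignoring the strata makes the t-test invalid. It only makes it slightly conservative, and gender is already in the regression. Levels well below 4.4% would need gender to explain far more of the variance than anything in the documents suggests.
- A reader might extend the point to all secondary outcomes. For cross-over the plan is "We will compare the difference in cross-over between groups using Pearson’s chi-squared test", a single test, so no pair competes there. The pairing recurs only for the continuous outcomes.

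It is also fair to say that the upper values of R² have no support in the documents. At the lower end the gain is about 2 points of power.

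**Conclusion.** The point holds as a low-cost improvement, not as an error that invalidates the analysis. The protocol article sets an unadjusted t-test and a multiple regression for one primary outcome and ranks them only by implication; the implied main test leaves out the stratification factor and the prognostic baseline data.

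Its size rests on assumed shares of explained variance. With R² of 5% to 30%, a baseline-adjusted model gains about 2 to 12 points of power over the t-test's 80%, and the two tests disagree in roughly one trial in twenty to one in seven. The conservatism of the t-test is minor, at most about 0.6 of a percentage point (5.0% − 4.4%) if gender explains up to 5%. The either-test error of 6.0% to 7.6% describes what an explicit rule would rule out; it is not the error rate of the plan as written.

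**What to change.** State in the protocol or the analysis plan, before the analyst is unblinded:

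- The single primary analysis is a linear model of lowest SpO2 on arm, gender (stratum), age, BMI and ASA class, reported as the adjusted mean difference with its 95% CI. This analysis decides superiority.
- The t-test is supportive.
- The same order applies to the continuous secondary outcomes that carry the same pair of tests (area under the curve of SpO2, ISAS score, mean and peak TcCO2).

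The covariates named here are those known before randomisation; procedure duration, hypotension and BIS are left out of the primary model for that reason.

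The cost is two or three sentences. All variables are already collected under {18a}, BMI following from height and weight. The 94 per group can stay: on the planning assumptions the adjusted model has about 80% power or more.

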In a number of indications, PSA is applied for longer periods. One of these indications is radiofrequency catheter ablation (RFCA) in AF patients with a duration a PSA of more than 3 h. AF ablation has become one of the most common procedures in the electrophysiology lab with rapidly increasing volumes. A recent survey by the European Heart Rhythm Association (EHRA) shows that in 2019, 32% of all procedures are performed under conscious sedation and 27.5% of all procedures under deep sedation [10]. The most commonly used hypnotic drugs were propofol and midazolam, whereas the most commonly used opioids were remifentanil and fentanyl [10]. The potential positive effects of HFNC in this growing patient population is unclear.

In the Maastricht University Centre patients undergoing RFCA are managed by deep sedation with a combination of low dose remifentanil and propofol, as patient movement may result in shifts of the electro-anatomical maps required for the navigation of the ablation catheter and might cause serious complications including air embolisms and cardiac tamponade. Deep sedation is associated with an increased incidence of upper airway collapsibility and disturbed central respiratory drive [13], which results in forced breathing movements during obstructive respiratory events resulting in pronounced intrathoracic pressure swings leading to electro-anatomical map shifts. Additionally, if LFNC is used (standard of care) a sudden drop of oxygen saturation (SpO_2_ < 90%) occurs in 1.5% of patients [17]. Increased pressure in the upper airway during HFNC might reduce upper airway collapsibility during sedation [21] and facilitates active gas exchange during times of hypoventilation [12] allowing stable and long PSA procedures. Additionally, HFNC may enhance carbon dioxide clearance by an entrained and highly turbulent supra-glottic flow vortices created by high-flow nasal oxygen and cardiogenic oscillations [12]**.**

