#### Intervention description {11a}

All randomised patients will receive standard care with regard to medications used for sedation and physiological monitoring or other interventions to support respiratory function that are considered necessary to be initiated during the procedure by the clinicians. Standard care is consistent with the ESA guideline on Procedural Sedation and Analgesia in Adults [14].

Deep sedation is defined as “A drug-induced depression of consciousness during which patients cannot be easily aroused but respond purposefully following repeated or painful stimulation”. Patients may require assistance in maintaining a patent airway, and spontaneous ventilation may be inadequate.

The physician assistant (PA) anaesthesiology or nurse anaesthetist (NA) administers a combination of analgesics and sedatives to target the level of deep sedation. There will be no restrictions of any dose ranges of the different medications used by the PA/NA. The actual doses of medication used will be registered. The PA/NA will record the doses of sedative medications used during procedures.

Oxygen therapy is administrated as indicated by randomisation. The device used for oxygen supplementation will be different.

For HFNC supplemental oxygen will be given with the Optiflow® device (Fisher and Paykel Healthcare, Auckland, New Zealand). The Optiflow® device has a heated breathing tube and chamber, and a nasal cannula will be used. The gas temperature will commence at high settings (37 °C) and titrated downwards if the patient complains of irritation. The gas flow rate will be started at 10 l/min prior to sedation. The gas flow rate of 10 l/min is usually well tolerated by awake patients. The gas flow will be increased after sedation has been administrated to 50 l/min. The gas flow can be titrated according to patients’ requirements. The flow rate is accommodated according to SpO_2_. The FiO_2_ will be set at 40%.

For LFNC, supplemental oxygen will be given with Microstream® Smart CapnoLine® O_2_. Oxygen supplementation is recommended to start at 5 l/min. The flow rate is accommodated according to SpO_2_. The clinician responsible for the sedation will in case of an upper airway obstruction combine the Microstream® Smart CapnoLine® O_2_ with a nasal or oral airway. The use of a nasal or oral Guedel airway is preferred above multiple airway repositioning to protect the clinician against unnecessary exposure to X-rays.

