#### Implementation {16c}

The allocation sequence will be generated by 2 members of the research team. After screening for eligibility, the patients can be allocated. The patients will be allocated on the day of treatment. The assigned allocation by the enrolling will be communicated to the physician assistant (PA)/nurse anaesthetist (NA) using sealed envelopes. The PA/NA performs the treatment which is assigned to the participant.

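### The adjusted linear regressions include procedure duration, hypotension and BIS, which arise after randomisation; if the device shifts them, the adjusted effect of HFNC can be biased in either direction.

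*Protocol article*

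**What the plan says.** In the Protocol article, Statistical methods {20a}, under Primary outcome, lowest SpO2 is analysed twice. The first analysis is described as "Univariable between-group analysis using the independent-samples" t-test. The second is introduced with its purpose: "To adjust for potentially confounding variables, we will perform multiple linear regression analysis". Its covariates are fixed: "Covariates will be age, gender, BMI, ASA-classification, duration of RFCA procedure, hypotension and BIS".

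Under Secondary outcomes, a regression follows the t-test for the continuous outcomes (SpO2 area under the curve, ISAS score, mean and peak TcCO2), with the same seven variables: "Covariates will be specified as age, gender, BMI, ASA-classification, duration of RFCA procedure, hypotension and BIS".

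On timing, Implementation {16c} states: "The patients will be allocated on the day of treatment". The sedation provider then delivers the assigned device. Plans for assessment and collection {18a} places the variables in the procedure itself: "Data from during sedation such as heartrate, blood pressure, bispectral index (BIS), duration of PSA and duration of procedure" come from the anaesthesia record. Intervention description {11a} treats hypotension as something that occurs, and is managed, during the procedure.

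**The concern.** Randomisation removes systematic confounding of the assigned treatment. A variable that arises after allocation cannot confound that comparison, but it can be a consequence of it. If the device changes such a variable, conditioning on it can remove part of the effect under test (mediation). It can also create an association through a shared unmeasured cause, such as how easily a patient's airway collapses (collider bias). The adjusted coefficient then no longer estimates the effect of assigning HFNC.

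The protocol supplies routes by which this could happen:

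- **BIS, and through dosing hypotension.** The sedation provider is unblinded (Who will be blinded {17a}), and on sedative dosing {11a} says "There will be no restrictions of any dose ranges of the different medications used by the PA/NA". Depth of sedation could therefore differ by arm.
- **Duration.** Background {6a} expects HFNC to reduce airway collapse and to help keep long sedations stable. It describes obstructed breathing as "resulting in pronounced intrathoracic pressure swings leading to electro-anatomical map shifts", which could affect how long the procedure takes. The Discussion reports more desaturation as procedure time grows, so duration is also tied to the outcome.

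The adjusted result is presented as the one that deals with confounding and could become the headline estimate.

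**Working it through.** **1. Classify the seven covariates by the protocol's own timing.**

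| Covariate | Source | Relative to allocation |
|---|---|---|
| Age, gender, BMI, ASA class | Baseline data, medical record {18a}; gender is the stratification factor {16a} | Before |
| BIS | Recorded during sedation {18a} | After |
| Duration of procedure | Recorded during sedation {18a} | After |
| Hypotension | Blood pressure recorded during sedation {18a}; managed during the procedure {11a} | After |

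No pre-sedation version of BIS or hypotension is defined.

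**2. Reproduce the planned sample size, to find the outcome SD it implies.** Sample size {14} gives means of 95.2% and 99.3% (difference 4.1 points), 80% power and alpha 0.05. With two-sided alpha and SD 10 points:

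n = 2 × (1.960 + 0.842)² × (10 / 4.1)² = 2 × 7.85 × 5.95 ≈ 93.4, so 94 per group.

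The printed SD of 0.1 gives 94 only if it is a fraction, that is 10 percentage points. That ambiguity is a separate matter. Here it means that results should be shown at SD 10 as well as at a smaller assumed SD of 3.

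**3. Bias formula.** In a linear model let *a* be the shift in the covariate caused by HFNC, and γ the covariate's coefficient in the adjusted model. Then

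adjusted effect = total effect − *a* × γ.

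If *a* = 0 there is no bias. The protocol gives neither *a* nor γ, so all values below are assumptions.

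**4. True total effect zero, 94 per group.**

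- HFNC patients 5 BIS points deeper, 0.15 SpO2 points per BIS point: 0 − (−5)(0.15) = +0.75.
- HFNC patients 3 BIS points deeper, 0.10 per point: 0 − (−3)(0.10) = +0.30.
- Duration as collider: HFNC shortens it by 15 min; one SD of unmeasured airway collapsibility adds 15 min and costs 1.5 SpO2 points; residual SD of duration 25 min. γ = −(15 × 1.5) / (15² + 25²) = −22.5 / 850 = −0.026, so the bias is 0 − (−15)(−0.026) ≈ −0.40. With residual SD 15 min it is −15 × 22.5 / 450 = −0.75.

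The approximate standard error of the difference is SD × √(2/94): 0.44 at SD 3 and 1.46 at SD 10. Two-sided rejection at the 5% level, from the normal approximation with bias / SE as the shift:

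| Bias | SD 3: bias/SE, rejection | SD 10: bias/SE, rejection |
|---|---|---|
| 0.75 | 1.71, about 40% | 0.51, about 8% |
| 0.30 | 0.69, about 10% | 0.21, about 5–6% |
| 0.40 | 0.91, about 15% | 0.27, about 6% |

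Simulation agrees: 41% and 10% for the two BIS cases at SD 3, and about 7–8% and 5–6% at SD 10. The SD 3 figures also depend on the assumed spread of BIS: 38% to 49% in the first case for a BIS SD of 6 to 10. The t-test stayed unbiased, with about 5% rejection.

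**5. True effect 4.1, SD 10, one standardised covariate.**

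- *a* = −0.2, γ = −3: 4.1 − 0.6 = 3.5.
- *a* = −0.5, γ = −3: 4.1 − 1.5 = 2.6.
- Collider, γ = −2.5: *a* = +0.3 gives 4.85; *a* = −0.3 gives 3.35.
- Both routes, γ = −5.5, *a* = −0.5: 4.1 − 2.75 = 1.35.

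The unadjusted estimate stays at about 4.1 in every case.

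**The case against.** The strongest reply has four parts.

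- **No shift is demonstrated.** Both arms are sedated to the same target of deep sedation, which limits a systematic BIS difference. No direct route from device to hypotension is documented: {11a} attributes haemodynamic fluctuation to heart-rate changes from the procedure and sedation, and vasopressor support is titrated against it. The route to duration is inferred, and the Discussion caps procedure time at 4 h. This stands. A reader might infer that the adjusted effect is certainly biased, but the documents support only that it can be.
- **The high rejection rates need an SD of 3.** That SD is not in the protocol, and at the SD that reproduces 94 per group the inflation is small. This stands, so the 41% must not be quoted alone. The zero-effect BIS scenarios also require a direct benefit exactly offset by deeper sedation.
- **A sound analysis is already planned.** Sample size {14} is for two independent means, the t-test comes first, and an explicit hierarchy may be in a statistical analysis plan that is not shown. This limits the damage. It does not justify the covariate list, which the article itself fixes.
- **Scope.** The list is attached to the primary regression and the continuous secondary outcomes only. The chi-squared test, the logistic or Poisson models and the Mann-Whitney tests are not given it.

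It is also tempting to fault the t-test for ignoring stratification by gender. It remains valid, at worst slightly conservative. Preferring a baseline-adjusted model, or adding a pre-oxygen SpO2 value, is a design preference rather than a correction.

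**Conclusion.** The point holds for the linear regressions of the primary outcome and the continuous secondary outcomes. Three of the seven covariates arise after allocation, and the stated reason for including them does not apply in a randomised comparison. If the device shifts any of them, the adjusted estimate can be biased in either direction.

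The size is conditional on assumed shifts: about 0.3 to 0.75 SpO2 points in the BIS scenarios, against a planned difference of 4.1. False rejection is then about 10–41% at SD 3 and 5–8% at SD 10. With a true effect of 4.1, the assumed scenarios gave adjusted estimates from 1.35 to 4.85.

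The documents do not support a claim that the trial's primary comparison is invalid. The t-test on which the trial is sized is untouched. What remains open in the article is which of the two analyses decides, and therefore whether the vulnerable one could become the main result.

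**What to change.** 1. In both regressions, restrict the covariates to variables fixed before randomisation: age, gender (as stratification factor), BMI and ASA class.
2. State which single analysis of lowest SpO2 is primary: the t-test on which the trial is sized, or the baseline-adjusted regression. Label the other as supportive.
3. Report duration, hypotension and BIS by arm. Use them otherwise only in a labelled exploratory or mediation analysis, or as auxiliary variables in the multiple imputation.

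The cost is a change of wording. No extra patients or measurements are needed, and 94 per group is unchanged because it rests on an unadjusted comparison of means. The one downside is slightly less residual variance explained in the adjusted model.

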### Sample size {14}

The sample size in this prospective study was calculated according to a similar study with the mean lowest SpO_2_ 95.2% (LFNC) and 99.3% (HFNC), with a standard deviation of 0.1 respectively in two different oxygen therapies [28]. Please note that this sample size is, although based on a similar study which compared the HFNC vs LFNC [8], also based on a different indication and with use of shorter (< 75 min) duration of treatment. To achieve 80% statistical power with α error rate of 0.05, the number of patients was calculated to be 94 for each group. An online statistical calculator, Statulator, was used to calculate the sample size for comparing two independent means.

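### The number of imputations is tied to the percentage of incomplete records with no minimum, so 1–2 incomplete records of 188 give m = 1, where Rubin's variance is undefined (minor)

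*Protocol article*

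**What the plan says.** The protocol article, Statistical methods {20a}, Primary outcome, states: "We will impute missing data using multiple imputation with fully conditional specification". The next sentence sets the size: "The number of imputations will be set to the percentage of incomplete records". The section on non-adherence and missing data {20c} repeats both sentences. Neither place gives a minimum, an expected percentage, or a definition of an incomplete record (primary-model variables only, or all trial variables including the questionnaires).

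The planned size is in Trial design {8}: "it is aimed to include 188 participants", with equal allocation. The adjusted primary model adds seven covariates to the outcome and treatment group: "Covariates will be age, gender, BMI, ASA-classification, duration of RFCA procedure, hypotension and BIS". All randomised participants are to be analysed, so a single missing value is enough to bring the rule into play.

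**The concern.** Scaling the number of imputations to the amount of missing data is a sensible idea, but here the percentage is the number itself and not a lower bound. When little is missing, m can fall to 1 or, with rounding down, to 0. Rubin's rules need at least two imputations to estimate the between-imputation variance. At m = 1 the stated method cannot be carried out, and a single imputation treats imputed values as if they had been observed.

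The case is plausible for the primary model. Lowest SpO2 comes from a continuous sensor recording, and the article draws the other variables from the medical record or the automatic patient data management system. A handful of incomplete records is a realistic outcome, though the article gives no rate.

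The second question is how much the primary p-value would move if the imputation were rerun with another random seed.

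**Working it through.** **Inputs.** N = 188 (Trial design {8}); the rule m = percentage incomplete ({20a} and {20c}). The article states no value of m and no expected missingness, so there is no stated figure for m to reproduce. The N behind the percentage does reproduce: with a difference of 4.1 points and the SD of 0.1 read as 10 percentage points, n = 2 × (1.96 + 0.8416)² × 0.1² / 0.041² = 93.4, i.e. 94 per group and 188 in total.

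**Step 1: the m that the rule gives.** For k incomplete records the percentage is 100k/188.

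| k | % | m, rounded down | m, nearest | m, rounded up |
|---|---|---|---|---|
| 1 | 0.53 | 0 | 1 | 1 |
| 2 | 1.06 | 1 | 1 | 2 |
| 3 | 1.60 | 1 | 2 | 2 |
| 4 | 2.13 | 2 | 2 | 3 |
| 6 | 3.19 | 3 | 3 | 4 |

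Every rounding convention has at least one k that gives m of 1 or 0.

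**Step 2: what fails at m = 1.** Rubin's total variance is T = U + (1 + 1/m)B, where U is the average within-imputation variance and B, the between-imputation variance, has divisor m − 1. At m = 1 that divisor is 0, so B and T are undefined. At m = 2 or 3 they are defined.

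**Step 3: size of the error at m = 1.** Assume the fraction of missing information (FMI) equals the incomplete fraction. Single imputation reports a variance proportional to 1 − FMI, while the true variance is proportional to 1 + FMI. The ratio of reported to true SE is √[(1 − FMI)/(1 + FMI)]:

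- one record, FMI 0.0053: √(0.9947/1.0053) = 0.995;
- two records, FMI about 0.01: √(0.99/1.01) = 0.990.

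The SE is 0.5–1% too small. With two records a nominal 5% test runs at about 5.2%.

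**Step 4: Monte Carlo error under the rule.** Relative to the SE it is about √(FMI/m). If m = 100 × FMI, this is √(1/100) = 0.10 whatever the missingness, and relative efficiency is 1/(1 + 0.01) = 0.990. For a p-value of 0.050, z = 1.96 ± 1.96 × 0.10 runs from 1.764 to 2.156, i.e. p from 0.078 to 0.031. At 3% incomplete, a minimum of 20 gives √(0.03/20) = 0.039, and a minimum of 50 gives √(0.03/50) = 0.024 (p about 0.045 to 0.056).

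**Step 5: simulation.** N = 188, outcome missing completely at random, complete-case p = 0.05, 600 repeat imputation runs per setting, Barnard–Rubin degrees of freedom (for m = 1, B ignored):

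| Incomplete | m by rule | SD of p | Central 95% of p | SD of p, m = 20 |
|---|---|---|---|---|
| 1% | 1 | 0.012 | 0.032–0.078 | 0.0025 |
| 2% | 2 | 0.015 | 0.031–0.087 | 0.004 |
| 3% | 3 | 0.015 | 0.031–0.087 | 0.005 |
| 5% | 5 | 0.013 | 0.031–0.081 | 0.006 |
| 10% | 10 | 0.014 | 0.029–0.084 | 0.010 |
| 20% | 20 | 0.016 | 0.029–0.093 | 0.016 |
| 30% | 30 | 0.015 | 0.028–0.085 | not needed |

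The run-to-run spread under the rule is about the same at 2–3% as at 20–30%. With a complete-case p of 0.03, between 93% and 98% of runs stay below 0.05 at every level.

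**The case against.** A reader might infer that the p-value is unstable because few records are missing. The working does not support that. The rule uses few imputations when there is little to impute, so relative Monte Carlo error stays near 10% of the SE throughout and the efficiency loss is about 1%. This objection stands in full.

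The 0.031–0.078 range is also near the upper end. The first primary analysis is an unadjusted t-test, and a missing BIS or ASA value makes a record incomplete without adding imputation noise to that test. In the adjusted model, gaps in covariates usually give an FMI below the incomplete fraction. This stands too, and it limits the seed effect to results near 0.05.

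Low missingness is itself assumed. The article plans reminders for questionnaire non-response. If those gaps count towards incomplete records, m could be well above 3. That makes m = 1 less likely but does not remove it, because the term is undefined and the rule has no lower limit.

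Finally, an analyst who found m = 1 would notice the conflict with multiple imputation and use more. That is likely, and it is why the point is minor. It would still mean departing from the written rule for the primary analysis after seeing the data. Nor is this a detail left to an analysis plan: the article fixes the rule explicitly, twice. A random seed, by contrast, is commonly left to the analysis plan, and its absence is no fault here.

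**Conclusion.** The concern holds in a narrow form. The rule fails outright when one or two of 188 records are incomplete (up to three if rounded down), because m is then 0 or 1 and Rubin's variance is undefined. A reader might infer materially wrong standard errors from this. The figures do not support that: the understatement is about 0.5–1%.

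As a separate and general point, the rule leaves seed-to-seed noise of up to about 10% of the SE at any missingness level. This rests on FMI equal to the incomplete fraction, and it is smaller if the gaps are mainly in covariates. It could change a conclusion only when p lies close to 0.05. Severity is minor.

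**What to change.** In both {20a} and {20c}, set the number of imputations to the larger of a fixed minimum and the percentage of incomplete records. A minimum of 20 or 50 would serve; the documents do not single out one value. Either removes the undefined case and makes the rounding convention irrelevant at low missingness. At 3% incomplete, a minimum of 20 cuts the SD of a p-value near 0.05 from about 0.015 to 0.005. A minimum of 20 changes nothing from 20% incomplete upwards, whereas 50 reduces the noise at any level below 50%. The cost is one phrase in each section and seconds of computing, with no effect on sample size or conduct.
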